**Control variables:**

The following socio-demographic variables will be documented: socio-economic status (family income

and parents’ employment status), country of birth of youth, country of birth of parents, ethnicity, years in Canada, language proficiency (English and French), migratory status (immigrants, refugee or citizen). In addition, contact with or use of mental health services outside of the school will be noted. A measure assessing the learning environment will allow us to control for the variance related to the

teacher and the school environment (inter-school variations). We will use the WIHIC (What Is Happening in this Class) questionnaire, developed by Aldridge and Fraser (106), to evaluate student cohesiveness, teacher support, involvement, task orientation, cooperation and equity in the class group. In a comparison with other learning environment measurement scales, it proved to be the instrument that provided the most explanation of inter-environment variance (107).

where E(C*t*)*theatre program* = the expected cost with the theatre program in the 12 week time period *t* (T0 – T1), E(C*t*)*tutorship* = the expected costs with the tutorship in the 12 week time period *t* (T0 –T1), E(C*t*)*regular class*= the expected costs with attending regular class in the 12 week time period *t* (T0 –T1), E(Eff*t*) *theatre program* / *tutorship* / *regular class* = the expected effectiveness with the theatre program, tutorship and regular class, respectively, corresponding to the change in SDQ symptoms in the specified time

period *t* (T0 – T1 or T0 –T2), because we will be evaluating symptoms at pre (T0), post (T1) and 9 months later (T2). These cost-effectiveness ratios will produce the cost for each unit change in student level of impairment which quantifies for decision makers the trade-off between costs and effects associated with these programs (112). In this context, we will consider the cost for an average change of

3.95 points in SDQ which represents a moderate effect size (d = 0.50) improvement in impairment.

**2.11 What is the proposed sample size?**

Ten classes per condition will be included in the study, with an estimated 18 students per class. Power

calculations were performed assuming: 1) a compliance rate of 80%; 2) 5% loss to follow-up at the end of the twelve-week program (T1); 3) within-class variance and residual variance estimated from the pilot data.

Power calculations were performed via simulation, using the above parameters and assuming a Normal distribution of change in SDQ scores over a range of possible effect sizes. Accounting for the within- class clustering of children using a linear mixed effects model with a random effect for class and a fixed effect for the intervention, the proposed sample size has 77.5% power to detect a moderate effect size (d

= 0.50), and 84.5% power to detect a 5 point difference in SDQ score between the theatre intervention and the control group. In the pilot study, there was a mean difference in change on the SDQ of 5.85 points between the intervention and control groups. However, the study participants were newly arrived immigrant and refugee youth who had been undergoing recent intensive stress. The type of symptoms tends to decrease relatively rapidly with time, even if the interactions significantly helped them to subside (113). In the present study, we will be working with youth presenting emotional and behavioural difficulties for a relatively long time, since this prompted their inclusion in special class. We thus expect that these chronic problems, although possibly more severe, may be more difficult to shift. Studies of psychosocial interventions are typically powered based on a moderate effect size (e.g., d = 0.50) to represent clinically significant change (e.g., (114)), Depression: management of depression in primary and secondary care. Clinical practice guideline No. 23. London: National Institute for Clinical Excellence). Thus, the study was powered to achieve at least a moderate (d =.50) effect size which corresponds to a 3.95 change in the SDQ impairment score.

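### Three sample-size figures in Protocol 2.11 (77.5% power at d = 0.50, 84.5% power at 5 points, and d = 0.50 equal to 3.95 points) cannot all hold for one design on one SDQ scale

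*Protocol*

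**What the plan says.** Section 2.11 sets the size of the trial: "Ten classes per condition will be included in the study, with an estimated 18 students per class". It allows for 80% compliance and 5% loss by the end of the programme, and takes "within-class variance and residual variance estimated from the pilot data", without giving their values. Power was simulated for Normally distributed change scores over a range of effects. The model was a linear mixed model with a random class effect and a fixed intervention effect.

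One sentence then gives two results for that design:

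- "the proposed sample size has 77.5% power to detect a moderate effect size", with d = 0.50;
- "84.5% power to detect a 5 point difference in SDQ score between the theatre intervention and the control group".

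The section ends by saying that the trial was powered for a moderate "effect size which corresponds to a 3.95 change in the SDQ impairment score". Section 2.10 uses the same conversion as its cost-effectiveness benchmark: "3.95 points in SDQ which represents a moderate effect size (d = 0.50) improvement in impairment".

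Section 2.11 does not state alpha, the SD of change, the two variance components or the number of simulation runs.

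**The concern.** By the protocol's own conversion, 5 points is 5/3.95 = 1.27 times the target effect. An effect that much larger should raise power well above 77.5%, yet the stated gain is only 7 percentage points.

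The 77.5% is the only support for the statement that the trial is powered for a moderate effect on its primary outcome. If 84.5% and the 3.95-point conversion are the sound figures, the trial has about a one-in-three chance of missing that effect. If the conversion is the faulty figure, the power statements stand but the benchmark in 2.10 is wrong.

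**Working it through.** **Inputs.** From 2.11: 77.5% at d = 0.50; 84.5% at 5 points; d = 0.50 equals 3.95 points (also in 2.10); 10 classes per arm; 18 × 0.80 × 0.95 = 13.68 analysed students per class. Assumed: two-sided alpha 0.05, and one SDQ scale for both point values.

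**Can each power be reproduced alone?** Not directly, because the variances are not given. Each can be reached with a suitable intra-class correlation (ICC). The conversion implies SD = 3.95/0.50 = 7.9. With SE² = (2/10) × 7.9² × [ICC + (1 − ICC)/13.68]:

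- ICC 0.104 gives 77.5% at 3.95 points and 93.0% at 5 points.
- ICC 0.165 gives 65.2% at 3.95 points and 84.5% at 5 points.

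These ICCs assume that d is scaled by the total SD. If d is scaled by the residual SD, they are about 0.09 and 0.13. On either scaling, no single ICC gives both stated powers.

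**Check without the ICC.** In one design the SE of the effect does not depend on the effect, so power = Φ(δ/SE − 1.960).

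1. From 77.5% at 3.95 points: δ/SE = 1.960 + 0.755 = 2.715, so SE = 3.95/2.715 = 1.455. At 5 points, 5/1.455 = 3.436, and power = Φ(1.476) = **93.0%** (stated 84.5%).
2. From 84.5% at 5 points: δ/SE = 1.960 + 1.015 = 2.975, so SE = 5/2.975 = 1.681. At 3.95 points, 3.95/1.681 = 2.350, and power = Φ(0.390) = **65.2%** (stated 77.5%).
3. If both powers are right, the effect detected with 77.5% power is 5 × 2.715/2.975 = **4.56 points**. Then SD = 4.56/0.50, about 9.1, and 3.95 is wrong.

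Put another way, going from 77.5% to 84.5% needs an effect 2.975/2.715 = 1.096 times larger. The stated effects differ by a factor of 1.266.

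**Other alphas.**

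| Alpha | Power at 5 points, given 77.5% at 3.95 | Power at 3.95 points, given 84.5% at 5 |
|---|---|---|
| 0.01 two-sided | 95.0% | 60.3% |
| 0.05 two-sided | 93.0% | 65.2% |
| 0.05 one-sided or 0.10 two-sided | 91.8% | 67.6% |
| 0.10 one-sided | 90.3% | 70.3% |

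Matching both stated powers would need a one-sided alpha of about 0.41.

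**Small-sample tests.** Noncentral t with 4 to 270 df predicts 92.3% to 93.0% at 5 points. A direct cluster simulation analysed on class means (20,000 runs per setting) gives 78% and 93% at ICC 0.08 with t on 18 df. With a 1.96 cut-off it gives 78% and 93% at ICC 0.10.

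**Compliance as dilution.** If the 80% means that a fifth of students receive no effect, simulation at ICC 0.04 gives 77% and 93%. Dilution shrinks both effects alike, so the conflict remains.

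**Simulation noise.** Both powers are multiples of 0.5%, which would fit 200 runs, but this is an inference. The best common fit to the two powers is 71.0% and 88.9%. Allowing for error in both, the likelihood-ratio p-value is 0.005 with 200 runs, below 0.0001 with 400, and 0.047 with as few as 100.

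**The case against.** The strongest objection is that three printed numbers conflict, not two. A reader might infer that at least one of the two powers must be wrong, or that power at d = 0.50 is either 77.5% or about 65%. The protocol supports neither reading. Both powers fit together if d = 0.50 is about 4.56 points, so the conversion may be the only error. Nothing in the text favours one explanation over another. This objection stands.

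A second objection concerns scale. Section 2.11 ties 3.95 to the impairment score but ties the 5 points, and the pilot difference of 5.85, only to the SDQ. Sections 2.8/2.9 separate the impairment measure (primary) from the SDQ global scores (secondary). If the 5 points is on another scale, the SD of 7.9 does not carry over and the conflict cannot be shown. This is possible but not what the text suggests: 2.10 calls the 3.95 points in SDQ, and 2.16 uses change in SDQ for the primary outcome. The same-scale condition still has to be declared, and the wording needs clarifying either way.

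Third, alpha and the number of runs are not given. The alpha range above shows that the first gap does not matter. Noise cannot be excluded, but if so few runs were used that noise explains the gap, the printed powers are too imprecise to rely on.

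Finally, the consequences for the design are limited. Ten classes per arm follows from two per arm in each of five schools (2.3), and no allocation, endpoint or analysis rests on these figures. That is correct. What is affected is the stated justification of sample size and, possibly, the benchmark in 2.10.

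**Conclusion.** The inconsistency is real. On one SDQ scale and in one design, 77.5% at d = 0.50, 84.5% at 5 points and d = 0.50 = 3.95 points cannot all hold. With two-sided alpha 0.05, keeping two of them changes the third as follows:

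- 84.5% at 5 points becomes about 93%;
- 77.5% at d = 0.50 becomes about 65%;
- 3.95 points becomes about 4.56.

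The conclusion does not depend on the ICC or on which SD defines d, because the points value is printed. It holds for one- and two-sided alphas from 0.01 to 0.10, where predicted power at 5 points is 90% to 95%. It rests on the two point values being on the same scale and on simulation noise not being the cause, which is unlikely (p about 0.005 if 200 runs were used). The protocol does not show which figure is wrong, so low power at the target effect is one possibility and not a finding.

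**What to change.** Re-run the simulation for the primary outcome, youth-reported SDQ impairment, with about 13.7 analysed students per class. State in 2.11 the alpha and its sidedness, the SD of change, the between-class and residual variances, and the number of runs. Say whether the 5 points and the 3.95 points are on the same scale. Then replace whichever of the three figures is wrong. If the points value for d = 0.50 changes, carry it into the cost-effectiveness benchmark in 2.10. If power at d = 0.50 proves to be about 65%, print that figure.

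The cost is one re-run of an existing simulation and edits to 2.11 and possibly 2.10. Correcting the text needs no extra classes or students.

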**1.3/1.4 Why is a trial needed now?**

Theatre therapy for teenagers is part of set of prevention programs developed in partnership with schools

(Sand Play Program at the preschool level, Arts and Stories at the elementary level, and Theatre at the secondary level). Qualitative evaluation of theatre expression workshops in classes for newly arrived migrants (French as second language) suggests that workshops are a safe expression space in which adolescents benefit from the support of their peers, the team and the ritual nature of the activity. The workshops promote the development and assimilation of the different transitional experiences associated with adolescence, migration and having a hybrid identity, and enable young people to transform, their experiences of adversity into a learning opportunity (Rousseau et al., 2005). The results of the quantitative evaluation, which compares students in welcome classes randomly distributed between experimental and control groups (n=123), revealed a significant reduction (p < 0.05) in the perception of distress and impairment associated with mental health symptoms experienced by adolescents who took part in the activity compared with adolescents in the control group (*ß* = -0.194). With respect to academic performance, results indicated a significant improvement (p < 0.05) in performance in math among the adolescents who took part in the activity compared with those in the control group (*ß* = -

0.167) (49). The teachers in the experimental groups also reported an increase in the general participation level of their students in class compared with the teachers in the control group.

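### The sample-size section does not establish power for the primary outcome: its score labels shift, and its figures conflict even if all are read as impairment points

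*Protocol*

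**What the plan says.** Protocol 2.8/2.9 makes youth-reported impairment on the SDQ Impact Supplement the primary outcome and lists the SDQ global score as a separate secondary outcome. Section 1.1 argues at length that impairment and symptoms are different things.

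Section 2.11 plans the trial as follows.

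- Size: "Ten classes per condition will be included in the study, with an estimated 18 students per class", with 80% participation and 5% loss by T1.
- Variability: "within-class variance and residual variance estimated from the pilot data". No SD, intraclass correlation (ICC) or significance level is printed.
- Variable simulated: change in SDQ scores, with no mention of impairment.
- Power, theatre against control: 77.5% at d = 0.50, and 84.5% at a difference of 5 points in SDQ score.
- Pilot: "there was a mean difference in change on the SDQ of 5.85 points between the intervention and control groups".
- Target: a moderate "effect size which corresponds to a 3.95 change in the SDQ impairment score".

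Section 2.10 describes the same number as "3.95 points in SDQ which represents a moderate effect size (d = 0.50) improvement in impairment". It defines effectiveness as change in SDQ symptoms, yet promises a cost per unit change in impairment.

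Section 1.3/1.4 reports the pilot in welcome classes (n = 123). It "revealed a significant reduction (p < 0.05) in the perception of distress and impairment associated with mental health symptoms experienced by adolescents" in the intervention group, with a coefficient of -0.194.

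**The concern.** The power statement is the only justification of the sample size for the primary hypothesis. It is useful only if the SD, the target difference and the class-level variance all belong to the Impact Supplement score. The labels leave open which score was simulated. The figures can be tested against each other, and they do not agree.

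Two things are at stake. The first is whether 77.5%, already below 80%, describes the primary comparison at all. The second is the argument in 2.11 that d = 0.50 is a cautious step down from the pilot. That argument needs the pilot effect and the target on one scale. The 3.95 is also carried into the cost-effectiveness analysis.

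**Working it through.** **Inputs (2.11 unless noted).** 10 classes per arm; 18 students per class; 80% participation; 5% loss; 77.5% power at d = 0.50; d = 0.50 equals 3.95 points; 84.5% power at 5 points; pilot difference 5.85 points. From 1.3/1.4: pilot n = 123, coefficient -0.194, p < 0.05. Assumed, because not stated: two-sided alpha of 0.05. ICC: not stated.

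**1. The plan's own figure.**

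- Implied SD = 3.95 / 0.50 = 7.9 (derived, not printed).
- Analysed per class: 18 × 0.80 × 0.95 = 13.68, or 136.8 per arm.
- Without clustering, SE = 7.9 × √(2/136.8) = 0.955, and power at 3.95 points is 98.5%.
- With clustering, SE = 7.9 × √[(2/136.8) × (1 + 12.68 × ICC)]. Power of 77.5% needs an ICC of about 0.104 (normal) or 0.085 (t, 18 df).

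So 77.5% is attainable, but it cannot be reproduced from what is printed.

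**2. The two powers against each other.** This check needs no SD, ICC or score range, only that 3.95 and 5 are points on the same score.

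- 77.5% at 3.95 points: SE = 3.95 / (1.960 + 0.755) = 1.455.
- Power at 5 points: Φ(5/1.455 - 1.960) = Φ(1.477) = 93.0%. The plan states 84.5%.
- Difference that gives 84.5%: (1.960 + 1.015) × 1.455 = 4.33 points.

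Noncentral t with 18 or 27 df also gives 93.0%. Across one-sided 0.05 and two-sided 0.025 and 0.01, power at 5 points runs from 91.8% to 95.0%.

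In reverse, 84.5% at 5 points implies SE = 5/2.975 = 1.681. That puts 77.5% power at 2.715 × 1.681 = 4.56 points, so SD = 4.56/0.50, about 9.1. Power at 3.95 points would then be Φ(3.95/1.681 - 1.960), about 65%.

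**3. Simulation error and rounding.** The number of runs is not stated. Assume as few as 200, so that the simulation standard errors are √(0.775 × 0.225/200) = 3.0 percentage points and √(0.845 × 0.155/200) = 2.6. The SE that best fits both powers is then 1.583, with true powers of 70.4% and 88.5%. The misfit is chi-square 7.9 on 1 df, p = 0.005, and it grows with more runs. Rounding does not help either: if the 5 were really 4.5 points, power would still be about 87%.

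**4. The pilot.**

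- 5.85 / 7.9 = 0.74 SD.
- Coefficient standardised to the SD of change, equal groups: d = 0.194 / √(0.5 × 0.5) = 0.39, or 0.39 × 7.9, about 3.1 points.
- Coefficient standardised to the T1 SD (equal SDs at T0 and T1): d on change = 0.388 / √[2(1 - ρ)], where ρ is the pre-post correlation. This is 0.39 at ρ = 0.5, 0.50 at 0.7, 0.61 at 0.8 and 0.73 at 0.86.
- Coefficient in raw points: 0.19 points.

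Only the T1-SD reading with ρ near 0.86 comes close to 0.74. The protocol gives neither the scaling nor ρ.

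**The case against.** The strongest reply is that *SDQ* is shorthand. Section 2.16 names the Impact Supplement as the primary outcome and in the same sentence speaks of average change in SDQ. Section 2.11 ends on the impairment score, and 2.10 ties its 3.95 to impairment. When the protocol means the symptom score, it usually says global scores. This stands as a possible reading, so loose labels alone would be a matter of wording. But it puts all the figures on one scale, and that is exactly where 77.5% at 3.95 and 84.5% at 5 conflict.

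The second reply is that a raw difference in change and a regression coefficient of unstated scaling, covariates and outcome form need not match. That is correct, and it limits the pilot comparison to *does not readily match*. Section 2.11 also does not cite the source of the 5.85; its description of newly arrived immigrant and refugee youth fits the welcome-class study.

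The third reply is that d = 0.50 rests on a convention for clinically significant change as well as on the pilot. That also stands: powering for a meaningful difference is legitimate.

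A reader might go further and infer that 0.50 exceeds the pilot impairment effect, so that power at the pilot effect is only about 56% to 58%. That holds only if the coefficient gives an effect of about 0.39 to 0.40 on change. From ρ of about 0.7 upward on the T1-SD reading, the pilot effect is 0.50 or more. A reader might also infer that 7.9 and 5.85 come from the SDQ global score, but nothing in the protocol assigns them to it.

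**Conclusion.** The point holds as a finding that power for the primary outcome is not established. On one scale, the stated 84.5% should be about 93% if 3.95 points has 77.5% power. Alternatively, d = 0.50 should be about 4.56 points rather than 3.95. At least one printed figure is therefore wrong, or the figures mix scores. This rests on 3.95 and 5 being points on the same score with the same SE. The assumed alpha moves the 93% only between 91.8% and 95.0%.

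The pilot mismatch is supporting evidence of lesser weight: 0.74 SD from the points, against about 0.39 to 0.73 SD, or 0.19 raw points, from the coefficient, depending on unstated scaling.

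The finding is that the stated power is unreliable, not that it is too low. Without the SD of change and class variance of the Impact Supplement, the true power could lie on either side of 77.5%. The correction should be made because the sample size rests on these figures and restating them is cheap.

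**What to change.** 1. From the pilot data, take the SD of change and the between-class variance of the self-reported Impact Supplement score. Print both, with the significance level.
2. State what d = 0.50 is in points on that score.
3. Re-run the simulation with those inputs and restate both power figures.
4. Correct or relabel 3.95, 5 and 5.85 in 2.10 and 2.11. If any of them belongs to the SDQ global score, say so and do not use it to justify power for the primary outcome.
5. In 2.10, use one outcome, impairment, for the effect in the cost-effectiveness ratio.

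The cost is a re-analysis of pilot data in hand and corrected wording, with no extra students. The downside is that the restated power may be less favourable.

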**2.12 What is the planned recruitment rate?**

At the start of the school year, the schools will send study participation consent forms to the parents and

assent forms to students. Based on the results of previous studies conducted by our team, we are expecting an overall participation rate of around 80% (20% refusing to take part).

**2.13 Are there likely to be any problems with compliance?**

In previous studies, non-compliance rates (failure to attend sessions) were so low that we didn’t need to

control for absenteeism, which we had initially planned to do to calculate an eventual dose/effect relation. The students in special classes enjoyed the pilot project workshops so much that the absenteeism rates observed in these pilot projects were extremely low. Absenteeism will nevertheless be tracked systematically and its effect on the program (tutoring and theatre) controlled if needed.

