**2.2.2. Group tutoring program:**

The theatre workshops will be compared with a program in the context of a self-contained classroom.

Students with emotional and behavioural difficulties (EBD) have been found to have comorbid academic and behavioural challenges (93, 94). Irrespective of the classroom placement (special or general education classes), the interventions for students with EBD almost exclusively focus on

behavioural management with academic learning being addressed secondarily, if at all (95). These students are often achieving significantly below level as compared to students without disabilities and exhibit underachievement in all academic areas (96). Research also consistently indicates that they do not improve over time and that in some areas (e.g., math) their difficulties increase (see review, (97)). Some subtypes such as externalizing behaviour and attention were more closely associated with academic underachievement. In addition, high school students with EBD in a self-contained setting indicated that overall school adjustment was predictive of academic performance (e.g., (98)). These interventions focused on targeting in-class academic skills associated with attention to the assigned task, good working habits, developing listening skills and academic reading in the classroom setting (93, 98-

100). Therefore, the comparison intervention of the proposed study is an academic in-class intervention that focuses on differentiated academic instruction and improved overall academic adjustment. Each self-contained class will include a core teacher who teaches curricula based on the Quebec Education Program with age appropriate competencies in reading, math, social studies and science content areas. In each classroom assigned to the tutorship intervention, two academic resource assistants will provide weekly in-class support to students for the same length of time than the drama workshop. Individualized student objectives on reading fluency and math will be implemented (one in math and one in reading per student), as it is believed that improvements in these areas will contribute to increased overall achievement, decreased absenteeism, and reduction in emotional and behavioural difficulties. These individualized student objectives will be met in the context of twelve sessions in a self-contained classroom setting.

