**2.16 Data analysis**

The effects of theatre intervention on the primary outcome, SDQ Impairment Impact Supplement, will

be assessed by comparing the average change in SDQ of children at the end of the 12-week intervention period in children in the theatre intervention to the children in the control group. The average change in SDQ of children in the theatre group will also be compared to the average change in SDQ for children in the tutorship group. These analyses will be performed using a linear mixed effects model (also called a hierarchical model), which will appropriately account for the within-classroom correlation of children. In addition to a term for the intervention group, the linear mixed effects model will also adjust for child age and gender.

Analyses of secondary outcomes will also be carried out using linear mixed effects models; these outcomes are: (a) change in impairment, self-rated at T2 (b) change in SDQ Global Scores, self-rated (c) change in SDQ Global Scores, teacher-rated (d) change in impairment, teacher rated (e) change in Adolescent Friendship Inventory (AFI) (f) change in School Performance. Analysis of the group x time interaction will be performed with the repeated measures (T0, T1, T2). All analyses will be conducted using the **R** statistical programming language, using the lme procedure to fit the linear mixed effects models.

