**2.18 Sub group analyses**

Analyses to determine the effect of gender and age will be conducted. In the pilot study, however, there

were no differential effects of treatment in the pilot study based on sex (p = .95) or age (p = .96). Thus, although we will control for a potential effect, we do not expect it to be significant. If classes and schools differ significantly on measured socio-demographic variables describing socio-economic and cultural variables we will include them as covariates in the outcome analysis to control for variation between groups/schools.

**2.19 Pilot studies:** The first and larger pilot study was done on regular and welcoming classes. No quantitative data was obtained in the subsequent piloting of the project in special class (90). Other pilot was recently realized (at the request of Québec Ministry of education) in special classes of under- schooled youth (n = 55). In these classes, the majority of youth have suffered high exposure to trauma and separation. This pilot results confirmed that self-report impairment decreased significantly with the intervention and that the intervention appeared to be more beneficial when exposure to premigratory hardship is high (89).

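### Section 2.18 adds covariates by a significance test between classes and schools, which is the wrong criterion, and section 2.13 does not keep absenteeism out of the primary contrast

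*Protocol*

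**What the plan says.** **Fixed part of the model.** Section 2.16 compares change in the SDQ impairment score between arms with a linear mixed model that allows for correlation within classrooms. It then says: "In addition to a term for the intervention group, the linear mixed effects model will also adjust for child age and gender". School is not named, and the T0 value enters only through the change score, not as a covariate.

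**Conditional socio-demographic covariates.** Section 2.18 gives a trigger, "If classes and schools differ significantly on measured socio-demographic variables", and a consequence: "we will include them as covariates in the outcome analysis to control for variation between groups/schools". Nothing exempts the primary outcome.

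**Absenteeism.** Section 2.13 reports that in previous studies "non-compliance rates (failure to attend sessions) were so low that we didn’t need to" control for absenteeism, which had been planned in order to study a dose/effect relation. For this trial it says: "Absenteeism will nevertheless be tracked systematically and its effect on the program (tutoring and theatre) controlled if needed".

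**Class environment.** The control-variables part of section 2.8/2.9 lists a learning-environment questionnaire "to evaluate student cohesiveness, teacher support, involvement, task orientation, cooperation and equity in the class group". It gives no measurement time for this score.

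**Allocation.** Section 2.3 draws two theatre, two tutoring and two regular-curriculum classes from each of five schools. Section 2.15 says that three of the schools are among the poorest on the Island and that the other two have a mixed population.

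**The concern.** A primary model should be settled before the data are seen. Its covariates should be chosen because they predict the outcome or were used in the randomisation. Section 2.18 instead chooses them by whether classes and schools differ significantly. Such a difference says nothing about whether the variable predicts change in impairment. It also says nothing about whether the theatre and control arms differ on it. The rule can add variables of no value and pass over useful ones. Meanwhile two obvious candidates are left out of the stated model: the stratification factor and the baseline score.

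Absenteeism raises a different problem. It is observed after allocation and may itself respond to the programme. Section 2.13 does not confine its use to a supportive analysis. If it entered the theatre-control comparison, the coefficient for theatre would no longer be the effect of being assigned to theatre.

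**Working it through.** The plan gives no figure for either rule, so there is none to reproduce. The stated 77.5% power comes from a model with a random class effect and a fixed intervention effect (section 2.11) and does not bear on the point.

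**1. Does the section 2.18 test measure arm imbalance?**
- Each school supplies 2 of the 10 classes in every arm. If school *s* has mean *x_s* on some variable, the mean over classes in any arm is Σ(2/10)·*x_s*, the same for all three arms.
- School differences therefore cancel between arms, apart from unequal class sizes and consent. A significant school difference is no evidence of confounding.
- Section 2.15 already describes the schools as socio-economically different, so the school half of the trigger may be met for reasons unrelated to bias.

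**2. How easily is the trigger met?** The 0.05 level, independence of the tests and the covariate intraclass correlations (ICC) below are assumptions.
- Class size: 18 × 0.80 = 14.4 consenting; 14.4 × 0.95 = 13.7 at T1. Use 14, in 30 classes.
- Simulated chance that a one-way ANOVA finds classes different on one covariate:

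| Covariate ICC between classes | P(significant) |
|---|---|
| 0 | 5% |
| 0.02 | 26% |
| 0.05 | 69% |
| 0.10 | 97% |

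- Section 2.8/2.9 lists 7 socio-demographic items, or 9 if income and employment, and English and French, are counted separately. With no true differences, the chance of at least one significant result is 1 − 0.95^7 = 30% to 1 − 0.95^9 = 37%.

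So the trigger fires often by chance, and nearly always under modest clustering. In neither case does it show that the arms differ.

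**3. What would adjusting for absenteeism do?**
- Section 2.13 equates non-compliance with failure to attend sessions. The control arm follows the regular curriculum without these activities (section 2.1), so session absence has no value there.
- To adjust theatre versus control at all, some absence measure common to both arms would be needed. Suppose one exists, that theatre shifts it by *a* SD, and that it relates to the outcome with coefficient *b*. With no shared causes, adjustment removes *a × b* SD of effect. If *a* = 0, nothing is removed.
- Illustration only: 20 classes of 14, SD 3.95/0.50 = 7.9, assumed ICC 0.12, true effect −3.95. Without adjustment the simulated estimate stays near −3.95. With *a* = 0, adjustment leaves it there, within simulation error of about 0.1. If theatre lowers absence by 0.2 SD, and absence affects the outcome (*b* of 0.2 to 0.4), shares a cause with it, or both, the estimate shrinks by about 0.3 to 1.0 points.
- The documents give neither *a* nor *b*, so this shows direction and mechanism, not an expected size.

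**The case against.** **Age and gender are fixed, and the added variables are background characteristics.** Both statements are correct. Adjusting for income, birthplace or migratory status removes no treatment effect, and the trigger does not look at outcomes. The section 2.18 rule is therefore not in itself a source of bias. The fault is a data-dependent model chosen on an irrelevant criterion.

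**The stated purpose in section 2.18 mentions groups, which may mean the arms.** It may. The trigger, however, is worded in terms of classes and schools, and it is the trigger that decides what enters.

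**Section 2.13 may intend only a dose/effect analysis.** This is the strongest objection. The sentence refers to the tutoring and theatre programmes, the earlier purpose was a dose/effect relation, and session absence does not exist in the control arm. A reader might infer that the protocol commits to adjusting the primary estimate for absenteeism and so biases it. The text does not say that. What stands is that the use is left open and should be closed.

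**Section 2.2.2 is weak support.** It expects that in tutoring "improvements in these areas will contribute to increased overall achievement, decreased absenteeism, and reduction in emotional and behavioural difficulties". A reader might take this as proof that absence mediates the primary contrast. It concerns the tutoring arm, which is outside that contrast, and reads as general school absence rather than missed sessions.

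**Class environment.** A reader might infer that a post-intervention score would be used as a covariate, adjusting away cohesion that the workshops aim to build. The protocol does not say so. Only a clarification of timing is warranted.

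**Loss of precision.** A reader might also fear many class-level covariates set against 20 classes. Most of the candidates are student-level variables, so that argument does not carry.

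**Conclusion.** The point holds as a fault in how the analysis is fixed, not as a demonstrated bias. Section 2.18 states a rule, so this is not detail left to a later plan. The rule makes the primary model depend on the data and tests differences between classes and schools, when school is balanced across arms by design. The stated model omits both school and the T0 score as covariates. Under the assumed 0.05 level and independence, the chance of a spurious trigger is 30% to 37%.

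For absenteeism the conclusion is conditional: if it were put into the theatre-control model, it could bias the estimate. The size is unknown. It is nil if absence does not differ by arm, and small if absence is as low as section 2.13 reports for the pilots. A percentage loss of the target effect could be produced only by assuming both the shift in absence and its relation to outcome, so none should be cited as a finding.

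**What to change.** 1. Section 2.18: delete the significance trigger.
2. Section 2.16: fix the primary covariates as T0 outcome, school, age and gender, whatever the baseline data show.
3. Report socio-demographic adjustment as one sensitivity model, with its variables listed in advance.
4. Section 2.13: state that absenteeism is used only in a separate exploratory dose-response analysis within the theatre and tutoring arms, and never to adjust the primary contrast.
5. Section 2.8/2.9: if the class-environment score is used as a covariate, use its T0 value only.

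**Cost.** These are wording changes. T0 scores, school, age and gender are already available, and the sample size is unchanged. The team gives up later choice of covariates. School as a fixed effect uses 5 − 1 = 4 between-class degrees of freedom: in the 20-class theatre-control contrast these fall from 20 − 2 = 18 to 18 − 4 = 14.
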